### Ethical approval

This study has been approved by the Medical Ethical Reviewing Committee of VU University Medical Centre, Amsterdam, The Netherlands (cf., protocol number 2011/327 and Central Committee on Research Involving Human Subjects, CCMO, protocol number NL37842.029.11).

### Study design

This protocol presents a parallel group, single-blind, superiority randomized controlled trial with pre-tests, post-tests, retention-tests and follow-up (Figure 2) to evaluate the relative efficacy of three intervention programs. Prior to randomization, pre-intervention assessments (T0) will be performed by one of two assessors within one week from informed consent. Subsequently, the assessor will randomly allocate (ratio 1:1:1) participants to one of three groups: 1) usual care (UC) control group, 2) conventional treadmill (CT) intervention group, 3) adaptability treadmill (AT) intervention group. We will use computer-generated block randomization with a block size of 21 participants to ensure equal group size after each block, with allocation concealment by opaque sequentially numbered envelopes that will be allocated serially to participants. An independent assessor blinded to group allocation will conduct post-intervention assessments (T1) within one week after completion of the intervention program. The same assessor will repeat these assessments 1 month later (retention assessments, T2). Follow-up assessments (T3) will be performed 12 months after completion of the intervention program. Furthermore, the incidence of trips, slips and falls will be monitored monthly between T1 and T3.

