## Methods/design

### Recruitment

All patients with a hip fracture admitted to residential and rehabilitation centre Zorggroep Solis, Deventer, The Netherlands will be assessed for eligibility within 3 days from admission by a physical therapist during regular intake. We aim to recruit 126 geriatric patients. Inclusion criteria are admission with a hip fracture related to falling, age ≥ 65 years, Functional Ambulation Category score 2 or higher (FAC, [34,35]), expected duration of admission ≥ 6 weeks and an ability to understand and execute simple instructions. Exclusion criteria are not being allowed to bear weight on the affected leg, moderate or severe cognitive impairments as indicated with a score below 18 at the Mini-Mental State Examination (MMSE, [36]), severe non-corrected visual impairments, contraindication to physical activity and an activity tolerance below 40 minutes with rest intervals. Patients eligible for participation will be informed of the current study by the physical therapist, both verbally and in writing. Patients who are willing to participate will be asked to give informed consent.

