### Intervention program

The intervention programs will be dose-matched in terms of duration (i.e., 40 minutes per session) and frequency (i.e., five sessions per week) of therapy over a 6-week inpatient intervention period. All intervention programs will be provided by physical therapists of Solis Zorggroep, Deventer, The Netherlands. Therapy sessions will typically be conducted by a single physical therapist with two participants per session; the two participants alternately exercise and rest, resulting in 20 minutes of practice per session. Physical therapists and participants cannot be blinded to group allocation.

In the *usual care* (UC) control group, participants will receive conventional physical therapy in all 30 sessions, consisting of exercises of upper-leg strength, balance, transfers, overground walking, and activities of daily living, following locally implemented guidelines of Solis Zorggroep, Deventer, The Netherlands and Deventer Hospital, Deventer, The Netherlands regarding the treatment of hip fractures.

In the *conventional treadmill* (CT) intervention group, participants will receive 15 conventional physical therapy sessions (as in UC) and 15 conventional treadmill training sessions (week 1-3: 2 per week, week 4-6: 3 per week) with an emphasis on repetitive stepping. Participants will walk at comfortable treadmill walking speed, without body-weight support other than handrail support. Comfortable treadmill walking speed will be determined at the beginning of each session in order to promote the quality and safety of walking as appraised by the physical therapist. The initial focus of conventional treadmill training will be on the quality and safety aspects of walking: therefore, therapists may give instructions regarding the walking pattern. After a safe walking pattern has been established, the focus will gradually shift towards walking faster and longer. Participants in the CT group will walk on the C-Mill treadmill (C-Mill, ForceLink, Culemborg, The Netherlands), but without projection of visual context on the belt’s surface.

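### A fixed, published block size of 21 at a single centre whose unblinded therapists also screen patients leaves a small, avoidable risk of selection bias at block ends

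*Protocol article*

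**What the plan says.** All references are to Methods/design in the protocol article.

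- **Recruitment.** Patients at the one centre "will be assessed for eligibility within 3 days from admission by a physical therapist during regular intake". The informing is done by the same profession: "Patients eligible for participation will be informed of the current study by the physical therapist, both verbally and in writing". Age, FAC and MMSE have numerical cut-offs. Other criteria need judgement, among them "expected duration of admission ≥ 6 weeks and an ability to understand and execute simple instructions", and on the exclusion side contraindication to activity and activity tolerance.
- **Study design.** The order is consent, T0, envelope: "Prior to randomization, pre-intervention assessments (T0) will be performed by one of two assessors within one week from informed consent". Then "the assessor will randomly allocate (ratio 1:1:1) participants to one of three groups", using "computer-generated block randomization with a block size of 21 participants to ensure equal group size after each block". The cards are hidden in opaque envelopes, numbered and used in order. No other block size and no stratification are described.
- **Intervention program.** Therapists of the recruiting centre deliver all three programmes, and "Physical therapists and participants cannot be blinded to group allocation".

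The article appeared in April 2013, is written in the future tense, and expects results in 2015. The block size was therefore public well before the results were due.

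**The concern.** Concealment depends on those who decide about the next patient being unable to foresee the next arm. Envelopes protect the individual card. They do not protect the end of a block whose length is known, because the remaining arms follow by subtraction.

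Here the people who screen belong to the same staff group at the same site as those who see which programme each participant receives, and the block length is in print. A therapist who knew that one arm was used up, or that only one was left, could judge a borderline patient in or out accordingly.

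The resulting imbalance would be hard to repair in analysis. The TUG and the three 10-metre walking tests are listed as primary outcomes but are not measured at T0. The Limitations section itself calls it a risky assumption that groups do not differ at T0 on such measures.

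**Working it through.** The article gives no figure for predictability, so there is none to reproduce. The block structure is consistent with the planned total: 126 / 21 = 6 blocks, 42 per arm.

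**Inputs.** Block of 21, three arms at 1:1:1, so 7 per arm (Study design); 126 participants (Recruitment). Assumed: the observer knows where each block starts and every earlier allocation in it. The last condition is then relaxed.

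**1. Allocations that are certain.** An allocation is certain when all 14 places of the other two arms have already gone. Among that allocation and those 14, it must come last, which has probability 1/15.
- Per block: 21 × 1/15 = 1.4
- Over six blocks: 8.4 of 126 = 6.7%
- Six of the 8.4 are simply the last place in each block.

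**2. Allocations with at least one arm ruled out.** For one given other arm, all 7 of its places precede the allocation with probability 1/8. For either of the two other arms: 2/8 − 1/15 = 0.1833.
- Per block: 21 × 0.1833 = 3.85
- Over six blocks: 23.1 of 126 (18%)

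**3. Participants still awaiting allocation.** Screening comes before consent, and T0 may be up to a week after consent, so an earlier participant may not yet have been allocated when the next is judged. Let R be the closing run of a single arm in a block (mean 1.4, at least 1). With one pending, the certain positions are R − 1: 1.4 − 1 = 0.4 per block. With two pending, subtract also P(R ≥ 2) = 6/20 = 0.3, leaving 0.1 per block. For step 2, at least two places always remain when the first arm runs out, so each of the first two pending participants removes exactly one position per block: 3.85, 2.85, 1.85.

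| Earlier participants pending | Certain, of 126 | At least one arm ruled out, of 126 |
|---|---|---|
| 0 | 8.4 | 23.1 |
| 1 | 2.4 | 17.1 |
| 2 | 0.6 | 11.1 |

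Simulation of permuted blocks gave the same values.

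**4. Overall guessing.** Always guessing the arm with most places left is right for 60.1 of 126 (47.7%), against 42 (33.3%) by chance.

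**5. Alternatives.**
- Smaller fixed, known blocks are worse. The number certain, of 126, is 42 for blocks of 3, 25.2 for 6, 18 for 9 and 14 for 12.
- With sizes drawn at random from 15, 18, 21, 24 and 27 and withheld, the tally alone makes no allocation certain. Guessing the arm used least so far is still right about 47.1% of the time (simulation). The gain is therefore at block ends, not in general guessing.

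**6. Replacement.** Sample size has non-adherent participants replaced, so more than 126 may be randomised. If 147 or 168 were (assumed), the upper bound would be 7 × 1.4 = 9.8 or 8 × 1.4 = 11.2.

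**The case against.** The strongest reply is that the knowledge required is nowhere documented. The article does not say that screening therapists know the block size, the boundaries or a running tally, nor that those who screen are those who treat. In week 1 the adaptability sessions resemble conventional treadmill training, so watching them would not separate those two arms. Replacement means that an observer would have to count everyone randomised, not only those retained. All of this stands, and it makes 8.4 an upper bound.

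The protocol also limits steering already. All hip-fracture admissions are assessed within 3 days, several criteria have cut-offs, consent and T0 precede the envelope, and the envelopes are opaque and used serially. Because that order is set, an extra eligibility sign-off before T0 would add little. A block of 21 is also less predictable than the smaller fixed blocks in step 5, and the authors give their reason for it, equal group sizes.

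Who generates and holds the list is detail that an article may leave to the full protocol, so silence on it is no fault. What remains is what the article does state: one fixed size, in print, at a site where unblinded staff of the same profession screen and approach patients.

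A reader might infer three stronger things, none of which the text supports:
- **About 8 allocations are certain whenever a patient is screened.** That needs a complete and current tally; one pending participant cuts it to about 2.4.
- **The assessor who allocates can steer enrolment or colour T0 scores.** The assessor has no stated role in eligibility. T0 is shared between two assessors, so neither need see the whole sequence, and biased scoring would be speculation.
- **The 48% guess rate is a fault of block size 21.** It barely changes with varied blocks, so it is a cost of balanced blocking in general.

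**Conclusion.** The point holds as a minor, avoidable weakness, not as evidence that enrolment was or would be steered. At most about 8 of 126 allocations (6.7%) could be deduced, and about 23 could have an arm ruled out. With one or two participants pending these fall to about 2.4 or 0.6, and to about 17 or 11. The figures rest on 7 per arm in each block, 126 randomised, and staff who know the block boundaries and follow the allocations. That last condition is an assumption: plausible at a single centre delivering every arm, but not stated. The change is worth making because it costs almost nothing, not because the expected bias is large.

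**What to change.** For the remaining allocations, replace the fixed block of 21 with block sizes varied at random around it, for example 15, 18, 21, 24 and 27. Have the list generated independently of the treating staff, and withhold the sizes from screening therapists and T0 assessors. Do not move to smaller fixed blocks, which would make more allocations deducible.

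The cost is a new computer-generated list and a new set of envelopes. The downside is that arm sizes may differ by a few participants when recruitment ends, which gives up the exact equality that the fixed block was chosen to secure.

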**Figure 2 F2:**
[figure not shown]
**Flow chart of the study procedures.** Abbreviations: AT = adaptability treadmill, CT = conventional treadmill, UC = usual care.

### Intervention program

The intervention programs will be dose-matched in terms of duration (i.e., 40 minutes per session) and frequency (i.e., five sessions per week) of therapy over a 6-week inpatient intervention period. All intervention programs will be provided by physical therapists of Solis Zorggroep, Deventer, The Netherlands. Therapy sessions will typically be conducted by a single physical therapist with two participants per session; the two participants alternately exercise and rest, resulting in 20 minutes of practice per session. Physical therapists and participants cannot be blinded to group allocation.

In the *usual care* (UC) control group, participants will receive conventional physical therapy in all 30 sessions, consisting of exercises of upper-leg strength, balance, transfers, overground walking, and activities of daily living, following locally implemented guidelines of Solis Zorggroep, Deventer, The Netherlands and Deventer Hospital, Deventer, The Netherlands regarding the treatment of hip fractures.

In the *conventional treadmill* (CT) intervention group, participants will receive 15 conventional physical therapy sessions (as in UC) and 15 conventional treadmill training sessions (week 1-3: 2 per week, week 4-6: 3 per week) with an emphasis on repetitive stepping. Participants will walk at comfortable treadmill walking speed, without body-weight support other than handrail support. Comfortable treadmill walking speed will be determined at the beginning of each session in order to promote the quality and safety of walking as appraised by the physical therapist. The initial focus of conventional treadmill training will be on the quality and safety aspects of walking: therefore, therapists may give instructions regarding the walking pattern. After a safe walking pattern has been established, the focus will gradually shift towards walking faster and longer. Participants in the CT group will walk on the C-Mill treadmill (C-Mill, ForceLink, Culemborg, The Netherlands), but without projection of visual context on the belt’s surface.

In the *adaptability treadmill* (AT) intervention group, participants will receive 15 conventional physical therapy sessions (as in UC) and 15 C-Mill gait adaptability treadmill training sessions (week 1-3: 2 per week, week 4-6: 3 per week) with an emphasis on practicing gait adaptability. As in CT, participants will walk at comfortable treadmill walking speed, without body-weight support other than handrail support. The two AT training sessions in the first week will consist of conventional treadmill training with an emphasis on the safety and quality aspects of walking (i.e., without visual context, similar to CT), so that participants will become acquainted to treadmill walking.

From week 2 onwards, AT training sessions progressively utilize the C-Mill’s visual context to elicit step adjustments (Figure 3 and Additional file 1). The gait adaptability exercises will be increased in difficulty from week to week to ensure that they remain sufficiently challenging. For reasons of safety and feasibility this will be done in a controlled fashion, tailored to the participant’s progress and ability. Specifically, in the second week of AT training, visually guided stepping to a sequence of stepping targets (Figure 3A) will be introduced to practice foot positioning relative to the environmental context projected on the belt. The spatial configuration of the sequence of stepping targets can be manipulated, requiring gait adjustments in terms of step length, step width and step-length symmetry. Furthermore, step adjustments can also be elicited on a step-to-step basis by introducing a degree of irregularity in the sequence of stepping targets. Consequently, each step needs to be planned and executed from scratch to ensure accurate foot placement relative to the stepping target. Visually guided stepping can be made more challenging by changing the degree of irregularity in the sequence of stepping targets and by scaling their size to the participants’ feet. In the third week, obstacle avoidance exercises will be included (Figure 3B) while continuing with the visually guided stepping exercises. Visual obstacles are projected onto the treadmill belt, and the difficulty level for obstacle avoidance will be controlled by the physical therapist by changing the size of the obstacle as well as the available response time (i.e., obstacles can appear a few steps ahead [easy] or during the swing phase of an ongoing step [difficult]). Obstacle avoidance is also evoked in the visually guided stepping exercises by introducing sudden target to obstacle shifts in the sequence of stepping targets, requiring an adjustment of an already planned step. From the fourth week onwards, participants will also practice speeding up and slowing down. To this end, a projected walking area of approximately 1 m^2^ will oscillate in anterior-posterior direction over the treadmill surface (Figure 3C). Participants will need to accelerate or decelerate relative to the fixed belt speed in order to follow the walking area; therapists can progressively or randomly vary the acceleration of the walking area to increase the difficulty of this speeding-up/slowing-down exercise. From the fourth week onwards, also so-called gait adaptability games will be introduced in the AT training sessions (Figure 3D). These gait adaptability games consist of interactive forest or beach trails scattered with stepping targets (e.g., beach balls) and obstacles (e.g., seals, shells, crabs). Participants can score or lose points depending on the successfulness of foot positioning relative to this environmental context. The interaction with the environment will be intensified further by means of direct feedback of stepping performance (e.g., the beach ball will pop forward if participants successfully step on it while a seal will scream loudly if participants accidentally step on it).

**Figure 3 F3:**
[figure not shown]
**Examples of C-Mill gait adaptability exercises.** Participants practice visually guided stepping to a sequence of regular or irregular stepping targets (**A**), obstacle avoidance (**B**), speeding up and slowing down by maintaining position in a moving walking zone (**C**), and all of the above in a functional and interactive gait adaptability game (**D**).

Note that we predict that the intensity of training, in terms of number of performed steps, will be markedly higher for both treadmill training intervention groups (i.e., AT and CT) than for the UC control group. We will test this prediction by comparing the number of steps taken per session among groups. To this end, the number of steps taken during AT and CT training sessions will be registered using the treadmill’s step counter while an observer will count the number of steps taken during UC sessions in a random sample of participants. We expect a main effect of Group in a one-way ANOVA, with post-hoc independent *t*-tests revealing significantly fewer steps for the UC control group than for both AT and CT training groups, in the absence of a significant difference between the latter groups.

To assist the therapist in progressively scaling the AT and CT training sessions, the participant’s perceived rate of fear and difficulty during AT and CT sessions will be assessed at a scale from 0 (no fear/not difficult) to 10 (much fear/very difficult), as well as their perceived rate of exertion using the 15 grade Borg scale (range 6-20, [37]).

Finally, adherence will be reported and the content of all individual training sessions will be registered by the supervising physical therapist. Adverse events during training sessions will be reported as well, and after completing the last UC, CT or AT therapy session of the intervention period, participants will fill out a purpose-designed questionnaire to register perceived discomforts during and after training sessions. The participant’s experience with the therapy program will be evaluated with this questionnaire as well to be able to compare the feasibility of the interventions from a participant’s perspective.

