This study protocol is designed to examine the efficacy of C-Mill gait adaptability training for improving walking ability and reducing fall incidence and fear of falling in older adults residing in inpatient rehabilitation care to recover from a fall-related hip fracture, a group particularly prone to falling [6-9]. The efficacy of C-Mill gait adaptability training will not only be contrasted against usual care, comprising of exercises in strength, balance, overground walking, transfers and activities of daily living, but also against intensity matched conventional treadmill training (i.e., without visual context presented on the belt), promoting repetitive stepping. Literature on conventional treadmill training in older adults recovering from hip injury is quite scarce, but generally positive with regard to its efficacy [32,33]. Conventional treadmill training outperforms overground gait training in that regard, most likely because of the enhanced intensity of training (i.e., defined in number of steps taken per training session). Older adults with a total hip arthroplasty, for example, performed 1000-1500 steps during a conventional treadmill training session compared to 100-150 steps during an overground gait training session of similar duration [32]. We therefore hypothesize that both conventional treadmill training and C-Mill gait adaptability treadmill training result in better outcomes related to walking ability than usual care due to the enhanced training intensity, with superior effects for C-Mill gait adaptability treadmill training on gait adaptability aspects of walking given the concurrent focus on practicing gait adaptability. The present study will thus shed light on the relative importance of high versus low practice intensity and adaptive versus repetitive stepping as key ingredients for effective intervention programs aimed at improving walking ability and reducing fall risk and fear of falling in older adults recovering from a fall-related hip fracture.

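### The step-count check cannot show that AT and CT were matched in intensity, and its comparison with UC contrasts session types, not the programmes as allocated

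*Protocol article*

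**What the plan says.** The Background (last paragraph) calls CT "intensity matched conventional treadmill training" and defines intensity as steps per training session. It uses the three arms to separate practice intensity from adaptive as against repetitive stepping.

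Under Methods/design, Intervention program (text following Figure 3), the article predicts that intensity "will be markedly higher for both treadmill training intervention groups (i.e., AT and CT) than for the UC control group". The data sources differ by arm. For the treadmill arms, "the number of steps taken during AT and CT training sessions will be registered" by the treadmill's counter. For UC, "an observer will count the number of steps taken during UC sessions in a random sample of participants"; the size of that sample is not given. The analysis is stated as "We expect a main effect of Group in a one-way ANOVA, with post-hoc independent" t-tests, with UC expected to be lower than both treadmill arms "in the absence of a significant difference between the latter groups". No margin or confidence-interval rule accompanies the AT-CT comparison, and no alpha is stated for it.

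The same section gives UC 30 conventional sessions. In AT, "participants will receive 15 conventional physical therapy sessions (as in UC) and 15 C-Mill gait adaptability treadmill training sessions", and CT has the same 15 and 15 split. Once CT participants walk safely, "the focus will gradually shift towards walking faster and longer". AT progresses through the difficulty of the stepping tasks.

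**The concern.** There are two separate weaknesses.

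1. **AT against CT.** The contrast isolates adaptive stepping only if the two arms take similar numbers of steps. Failing to find a difference is weak evidence of similarity when the test could easily miss a relevant gap. If AT takes more steps and the gap goes unseen, an intensity effect may be read as an adaptability effect. If CT takes more, a real adaptability benefit may be masked. The article's own cue, CT moving to faster and longer walking, points to masking.

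2. **Treadmill arms against UC.** The prediction is about groups, but the counts for AT and CT come only from treadmill sessions, which are half of each programme. The other half is conventional therapy of the kind UC receives. Outcomes are compared between whole programmes, so the intensity contrast used to explain them should be on that scale too.

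**Working it through.** The article gives no power or precision figure for this check, so there is none to reproduce. The POMA sample size is not in dispute.

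**A. What the AT-CT test can detect**

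Inputs:
- 126 participants allocated 1:1:1 (Sample size; Study design), so 126/3 = 42 per arm.
- Mean of 1,250 steps per treadmill session, the midpoint of the 1,000 to 1,500 quoted in the Background from a study of total hip arthroplasty patients.
- SD not given; 125 to 500 steps is assumed.
- Alpha not stated for this check; 0.05 is assumed, with 0.017 (the Sample size value) alongside.

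Detectable difference at 80% power, normal approximation: (1.960 + 0.842) × √(2/42) = 2.802 × 0.218 = 0.61 SD. With the t distribution it is 0.62 SD, or 0.72 SD at alpha 0.017.

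Chance that a true gap is non-significant (two-sample t-test, 42 per arm):

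| Assumed SD | 10% gap (125 steps), alpha 0.05 | 10% gap, alpha 0.017 | 15% gap (187.5 steps), alpha 0.05 | 95% CI half-width (steps) |
|---|---|---|---|---|
| 125 | 0.5% | 1.7% | under 0.1% | 54 |
| 250 | 38% | 55% | 7.5% | 109 |
| 375 | 67% | 81% | 38% | 163 |
| 500 | 80% | 90% | 60% | 217 |

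The answer depends heavily on an SD that nobody can read off the article. The confidence interval would show the precision actually reached; the p-value alone would not.

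**B. Treadmill arms against UC**

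Let t be steps per treadmill session and u steps per conventional session.
- UC programme: 30u, mean u per session.
- AT or CT programme: 15t + 15u, mean (t + u)/2 per session.
- Planned difference: t − u. Programme difference: (t + u)/2 − u = (t − u)/2. The planned figure is twice the programme figure for any t and u.
- Planned ratio: R = t/u. Programme ratio: (R + 1)/2.

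With the Background's figures (treadmill 1,000 to 1,500; overground 100 to 150; midpoints 1,250 and 125):
- AT or CT: 15 × 1,250 + 15 × 125 = 18,750 + 1,875 = 20,625 steps.
- UC: 30 × 125 = 3,750 steps.
- Programme ratio 20,625/3,750 = 5.5, against a session ratio of 1,250/125 = 10. Overstatement 10/5.5 = 1.82-fold.
- Across all pairings of the two ranges the overstatement is 1.74 to 1.88-fold. If the true session ratio were only 2, it would be 2/1.5 = 1.33-fold.

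The doubling assumes that all 30 sessions are attended and that conventional sessions yield the same steps in every arm. Four completed weeks suffice for inclusion. A participant who stopped there would have had 2 + 2 + 2 + 3 = 9 treadmill sessions out of 20, and the factor on the difference would be 20/9 = 2.2.

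**The case against.** The strongest case on the other side has four parts.

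- **Matching is largely by design.** AT and CT share the treadmill, the weekly schedule, session length, comfortable walking speed and therapist-led progression, and the first week of AT resembles CT. The t-test checks this and is not its only support. This stands, but equal minutes at a self-selected speed do not fix step counts. CT's stated progression and AT's manipulation of step length both leave room for a gap.
- **The article states an expectation, not a rule for declaring equivalence.** This is fair: a reader might infer that non-significance is to be taken as proof of matching, and the text does not say so. It is nevertheless the only criterion offered for a property that the Background asserts.
- **Intensity is defined per session, so the planned comparison fits its definition.** This also stands. It is a valid contrast of session types, and 5.5-fold would still be markedly higher. What remains is that the prediction is worded for groups.
- **The numbers are soft.** The step counts come from a cited example in another population, while UC here mixes walking with strength, balance, transfer and daily-living exercises. The SD is assumed, and at 125 steps a 10% gap would hardly ever be missed. All of this is correct, so the figures are illustrations and ranges, not forecasts.

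**Conclusion.** The point holds in a limited form. A non-significant AT-CT test would not establish matched intensity: power reaches 80% only at about 0.62 SD with 42 per arm, and the miss rate for a 10% gap runs from 0.5% to 80% over the assumed SDs. The planned UC comparison, read as a contrast of allocated programmes, doubles the per-session difference under full adherence and equal steps in conventional sessions. At the illustrative 10:1 figures it turns a ratio of 5.5 into 10.

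Three stronger readings are not supported:
- A reader might infer that the check will wrongly credit adaptability. The direction is open, and the only directional cue in the text points to masking an AT benefit.
- A reader might infer a flat two-fold exaggeration. That applies to the difference scale only, and only for programmes; on the ratio scale it is smaller.
- A reader might infer that the trial's results are compromised. The planned analyses of primary and secondary outcomes do not use the step counts. What is affected is the explanation given for those results.

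**What to change.** 1. **AT against CT.** Compute one value per participant, the mean steps per treadmill session. Report the AT/CT ratio of means (or the difference) with a 90% confidence interval against a margin fixed and justified beforehand, for example 0.80 to 1.25. Call intensity matched only if the whole interval lies inside; otherwise report it as not shown. For a rough idea of feasibility, take a difference margin of 250 steps (20% of 1,250), truly equal arms and 42 per arm. The interval would lie inside with probability of about 99.6%, 84% and 47% at SDs of 250, 375 and 500. With a margin of 125 steps it would be about 47% even at SD 250.

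2. **Treadmill arms against UC.** Keep the planned comparison but label it a contrast of session types. Use an unequal-variance test, with the UC side limited to the sampled participants.

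3. **Programme-level estimate.** Add mean steps over all 30 sessions, applying the mean of the sampled UC participants to the conventional sessions of AT and CT, and state that assumption. Because the same UC mean then enters both sides, the difference is half the session-type difference. Its confidence interval should be halved likewise, so that the imputed sessions are not treated as known.

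**Cost.** A few lines of analysis wording and a small calculation on data already planned; no extra participants. The intensity contrast will look smaller, and matching may come out inconclusive. The outcome analyses stay as they are.
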